#### Glycemia, Gestational Diabetes, and Insulin Resistance

A blood sample is drawn after an overnight fast, and glucose, insulin, and lipid profile (triglycerides and high-density and low-density lipoprotein cholesterol) will be analyzed at the Department of Clinical Chemistry, Linköping University Hospital. Furthermore, systolic and diastolic blood pressure will be assessed in a resting state, following standardized procedures. Gestational diabetes is defined according to the International Association of Diabetes and Pregnancy Study Group’s cutoff [34]. Furthermore, insulin resistance, as assessed by the HOMA-IR (homeostasis model assessment - insulin resistance) will be calculated according to the study by Matthews et al [35].

### Other Measurements

#### Demographic Information

The women and their partners complete separate demographic questionnaires, which include information regarding age, country of birth, occupation, educational attainment, previous pregnancies, smoking habits, dietary and physical activity habits, overall health, and use of medications.

#### Physical Fitness and Subjective Physical Activity

Cardiorespiratory fitness is assessed using the 6-minute walk test, which measures the maximum distance (in meters) the woman can walk in 6 minutes back and forth in a 30-m corridor [36]. Participants are instructed to walk as fast as possible during the test, but they are also informed that they may slow down or rest, if necessary. The 6-minute walk test is only conducted at the baseline measurement, whereas all other measures of physical activity and fitness will be conducted both at the baseline measurement and at gestational week 37. Upper body muscular strength is measured using the handgrip strength test, where the woman is asked to squeeze a dynamometer (TKK 5001; Grip-A, Takei, Tokyo, Japan) as hard as she can with her hand for a few seconds [37]. Physical fitness is also assessed subjectively using an adapted version of the international fitness scale, which includes cardiorespiratory fitness, muscular strength, speed and agility, flexibility, and overall fitness using 5-point Likert-scale questions [38]. As a complement to the objective physical activity data, we also collect data of subjective physical activity using two questionnaires: the short-form International Physical Activity Questionnaire, where participants recall their physical activity over the past 7 days [39], and a 7-day modified version of a questionnaire used by Bexelius et al [40].

#### Maternal and Infant Body Fatness Postpartum

At 1-2 weeks postpartum, maternal body fatness is measured using air-displacement plethysmography (as described above) utilizing suitable postpartum fat-free mass density values [32]. At the same time, infant body composition is measured using air-displacement plethysmography (Pea Pod, COSMED), as described in detail previously [22]. Briefly, body weight and body volume are measured by the Pea Pod. Body fatness is then calculated using the measured body density and appropriate fat-free mass hydration factors [41].

#### App Usability and Process Evaluation

Participants in the intervention group will complete a questionnaire including questions on their use and perception of the app with regard to usability, design, features, and overall satisfaction. Furthermore, semistructured interviews (audio) will be conducted within a subsample (n=10-20) of women in the intervention group to gain additional insight about their perceptions of the HealthyMoms app. The interviews will be transcribed and analyzed using thematic analysis, as described elsewhere [42].

### Statistical Analyses

Imputed data will be continuously checked against source data, and range checks will be implemented. The primary outcome will be gestational weight gain (kilogram). Analyses will be conducted according to the principles of intention-to-treat and per-protocol procedures using independent *t* tests to test whether gestational weight gain is statistically different between the groups. In the intention-to-treat analysis, missing data will be imputed using multiple imputations with chained equations [43]. In the per protocol, patients will be defined as completers if they have gestational weight gain data (body weight measured at baseline and gestational week 37) and if they have downloaded and used the HealthyMoms app at least once. Furthermore, linear regression will be considered to adjust estimates for the pre-pregnancy body mass index group (ie, underweight and normal weight vs overweight and obese), socioeconomic status (university degree vs no university degree), and parity (0 vs ≥1). In this analysis, treatment will be used as a categorical variable, with the control group as the reference. This model will also be extended to include interactions (one at a time) of the treatment with the pre-pregnancy body mass index, socioeconomic status, and parity, since we want to investigate whether the effect of the intervention differs depending on these factors. In a sensitivity analysis, we will also exclude women diagnosed with gestational diabetes and pre-eclampsia before the follow-up measurement, since these women may have received intensive diet/physical activity support or medication or may have edema, all of which may influence the outcome variables (eg, body weight, diet, physical activity, and glycemia).

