### Sample Size and Power Considerations

Power for an independent *t* test was calculated *a priori* using G*Power 3.1 [20]. A total of 226 women (113 in each group) completing the measurements after the intervention provides 80% power (α=.05, two-sided), assuming a common SD in gestational weight gain of 4 kg [21] to detect a difference of 1.5 kg between the groups. Given our previous experiences [22], we anticipate that no more than 25% of the women will drop out of the study or have a child prematurely. Thus, we will recruit 300 women (150 in each group) to participate in the study.

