### Primary outcome

#### Gestational Weight Gain

The primary outcome gestational weight gain is calculated as the measured body weight in gestational week 37 minus the measured body weight in gestational week 14. Body weight is recorded using standardized procedures when the participant is wearing only underwear. We will also analyze gestational weight gain as within or above the Institute of Medicine-recommended levels by using the recommended weekly gains in body weight during the second and third trimester [1].

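### The primary weight-gain comparison is an unadjusted t test and baseline adjustment is left optional, which forgoes precision the trial could have at almost no cost

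*Protocol article*

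**What the plan says.** The protocol article, under Gestational Weight Gain, defines the primary outcome as the "measured body weight in gestational week 37 minus the measured body weight in gestational week 14".

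Under Statistical Analyses, the groups are compared on this outcome by independent t tests, in an intention-to-treat analysis with multiple imputation and in a per-protocol analysis. The section then adds that "linear regression will be considered to adjust estimates for the pre-pregnancy body mass index group", along with socioeconomic status (university degree or not) and parity (0 or at least 1). The coding of all three covariates is given, and each has two levels. The text does not say when the regression would be run or how its result ranks against the t test. The same model is then to be extended, in firm wording, with treatment interactions one at a time.

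Sample Size and Power Considerations is written for the same t test. Its headline statement is "A total of 226 women (113 in each group) completing the measurements after the intervention provides 80% power". The other inputs there are a two-sided significance level of 0.05, an SD of 4 kg that is not reduced for any covariate, and a between-group difference of 1.5 kg.

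**The concern.** Under Randomization and Blinding, allocation follows the baseline measurement, so week-14 weight is known for every woman before she is allocated. The investigators have themselves picked out BMI group, education and parity as factors worth adjusting for. The Content and Use section gives one reason to expect BMI to matter, since the app derives each woman's recommended gain from it. The randomisation is described as blocks of 2, with no stratification factor mentioned, so nothing described in the design balances these factors between the groups.

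Two things are at stake.

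- **Precision.** Any outcome variance that the covariates explain is left in the residual of the t test. Recovering it narrows the confidence interval and raises power without recruiting anyone. Adjustment also corrects for chance imbalance in the same factors.
- **Commitment.** The adjusted estimate is optional, while the interaction analyses built on the same model are promised. A reader of the results could not tell from this article whether an adjusted estimate was due, or what weight it should carry.

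**Working it through.** **Inputs.** From Sample Size and Power Considerations: difference 1.5 kg, SD 4 kg, two-sided alpha 0.05, 113 per group. The share of outcome variance explained by the covariates (R²) is not in the document. I assume 0.02, 0.05, 0.10 and 0.20.

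**1. The plan's own figure.**

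- Standard error = SD × √(2/n) = 4 × √(2/113) = 0.532 kg.
- Noncentrality = 1.5 / 0.532 = 2.819.
- The two-sided critical t on 224 degrees of freedom is 1.971.
- The noncentral t distribution gives power of 80.1% at 113 per group and 79.8% at 112.

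The stated 113 per group is therefore reproduced exactly.

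**2. Slack in recruitment.** The article states that "we anticipate that no more than 25% of the women will drop out of the study or have a child prematurely" and that "we will recruit 300 women (150 in each group) to participate in the study". 300 × 0.75 = 225, against 226 required. This agrees to within rounding, but leaves no margin above 80%.

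**3. Power with adjustment.** Residual SD = 4 × √(1 − R²). The noncentrality is recalculated with this SD. The degrees of freedom are 226 − 2 − 3 = 221 for the three covariates named in the article. The half-width of the 95% confidence interval is the critical t times the standard error.

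| Assumed R² | Residual SD (kg) | Standard error (kg) | Noncentrality | Power at 113 per group | n per group for 80% | 95% CI half-width (kg) |
|---|---|---|---|---|---|---|
| 0 (t test) | 4.000 | 0.532 | 2.819 | 80.1% | 113 | 1.05 |
| 0.02 | 3.960 | 0.527 | 2.847 | 80.9% | 111 | 1.04 |
| 0.05 | 3.899 | 0.519 | 2.892 | 82.1% | 108 | 1.02 |
| 0.10 | 3.795 | 0.505 | 2.971 | 84.1% | 102 | 0.99 |
| 0.20 | 3.578 | 0.476 | 3.151 | 88.1% | 91 | 0.94 |

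Adding week-14 weight as a fourth covariate leaves 220 degrees of freedom. At 113 per group the power and half-width figures are the same to the decimals shown, so the cost of estimating the covariates is negligible.

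**4. Reading the table.** The gain runs from 0.8 percentage points (R² 0.02) to 8.0 points (R² 0.20). In sample-size terms it is worth between 113 − 111 = 2 and 113 − 91 = 22 evaluable women per group.

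**The case against.** The strongest reply is that nothing is wrong. An unadjusted comparison is valid under 1:1 randomisation, and the trial was powered for exactly this test and reaches its 80%. The regression enters as an addition meant to adjust estimates, with its covariates, coding and reference group already fixed. All of that stands, and it is why the point concerns efficiency and commitment only.

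A reader might infer more: that the deciding model stays open until the data are seen, and that type I error is inflated as a result. The article does not support this. Both the power section and the analysis section name the independent t test, so the primary test has a clear default. In a null simulation that always reported the smaller of the unadjusted and adjusted p values, type I error was about 6.5% to 7.6% for assumed R² of 0.05 to 0.30. Nothing in the article says results will be chosen that way, so those figures do not describe this plan.

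Four narrower objections also carry weight.

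- The size of the gain is unknown. A BMI-based recommendation for weight gain shows that BMI is a plausible predictor, but not how much variance in actual gain it explains. At R² of 0.05 or less, the gain is about 2 points or fewer.
- The source of pre-pregnancy BMI is not stated. Women are identified in the first trimester, so the trial cannot have measured it itself. A continuous value should be requested only where one exists.
- Week-14 weight and pre-pregnancy BMI probably overlap, so their separate contributions cannot be assumed to add up.
- No defect has been shown in the analysis of the secondary outcomes, so the point does not extend to them.

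An unseen analysis plan may hold further detail. The article does, however, take a position on adjustment, and it is that position which is loose.

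**Conclusion.** The point holds as a modest, worthwhile improvement. The primary analysis leaves out baseline information that the investigators regard as relevant, and it makes the adjusted estimate optional. The likely benefit is about 1 to 8 percentage points of power for R² between 0.02 and 0.20, or a confidence interval half-width of 1.04 down to 0.94 kg in place of 1.05 kg. These figures rest on the article's own SD of 4 kg and difference of 1.5 kg, on 113 evaluable women per group, and on R² values that are assumed. The stated sample size is correct, and the planned t test would give a valid answer.

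**What to change.** Before the final analysis, replace the conditional wording with a commitment to one linear model of weight gain from week 14 to week 37 on:

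- treatment, with control as the reference;
- week-14 weight;
- pre-pregnancy BMI, continuous where a value is available and otherwise in the stated two groups;
- parity (0 or at least 1);
- university degree (yes or no).

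Fit it in the intention-to-treat set, pool it over the multiple imputations, and name it as the primary estimate. Report the unadjusted t test as supportive. Keep the two-level BMI group for the interaction analysis.

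The cost is a change of wording in the analysis plan, plus a check on where pre-pregnancy BMI comes from. No new measurement or change in recruitment is needed. When the article was published, 190 of the planned 300 women had completed baseline and follow-up was expected to run to June 2020, so there was time to fix the model before the final analysis. Because the change replaces the test for which the trial was powered, it should be dated and documented as made before any comparison of outcomes between groups.

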### Ethical Approval

The HealthyMoms trial was approved by the Regional Ethical Review Board in Linköping, Sweden on April 24, 2017 (DNR: 2017/112-31), with an amendment on May 4, 2018 (DNR: 2018/262-32). All women will provide written informed consent before entering the study. The mother and father/partner will provide informed written consent before any measurements of their infant are performed.

## Results

The HealthyMoms app was finalized in September 2017. Recruitment of participants to the trial was initiated in October 2017, and 190 women have so far completed the baseline measurement. The baseline measurements are estimated to be finalized in December 2019, whereas the follow-up of the mothers and infants is estimated to be completed in June 2020.

## Discussion

The HealthyMoms trial will examine whether a novel mHealth app can mitigate excess gestational weight gain and promote healthy dietary habits, physical activity, healthy levels of body fatness, and normal glycemia. The trial has several strengths including the objective and accurate methodology to measure physical activity and body composition, close collaboration with existing maternity health care services, and a large sample size. The latter represents a distinct strength, considering that previous studies that have investigated the effect of a mHealth app on gestational weight gain have been relatively small pilot studies, although some have shown promising results. For instance, in a study of 100 overweight and obese Australian women, Wilcox et al [44] found that women in the intervention group had significantly lower gestational weight gain than women in the control group. Similarly, in a trial of 54 overweight/obese American women, Redman et al [45] found lower gestational weight gain in those receiving an intensive intervention delivered in-person or via smartphone as compared to those receiving usual care [45]. However, Chao et al [46] did not find any effect of a telemedicine intervention on gestational weight gain in 41 American women with overweight or obesity. Hence, the HealthyMoms trial will make an important contribution to the existing literature, considering the study size and that normal weight women are included in the study. This is important because excessive gestational weight gain is common among women having normal weight before pregnancy [1,3]. Finally, the intervention content is grounded in the social cognitive theory [16] and uses well-recognized behavior change techniques [17].

The HealthyMoms trial also has several limitations. First, although all eligible women are approached to enter the study, it is possible that an overrepresentation of highly educated, health conscious, and normal-weight women enter the trial. However, we will also examine whether there are any differences in the effect of the intervention in terms of maternal pre-pregnancy body mass index, educational attainment, and parity. Second, due to the time and budget constraints, we did not individually tailor push notifications; however, women have an individually tailored weight gain chart depending on their pre-pregnancy body mass index. Third, due to the thorough baseline measurement and to ensure that most women would be able to participate in the trial, women will receive the HealthyMoms app in gestational week 15. However, if the app is proven effective, an earlier introduction in pregnancy should be considered when fully implementing the app as a supportive tool in maternity health care. Finally, women need to be able to speak and read Swedish sufficiently well to understand the content of the HealthyMoms app in order to be eligible for participation. Hence, we aim to translate and modify the HealthyMoms app in order to make it widely accessible.

Excessive gestational weight gain is a major public health issue globally [1,2] and in Sweden [3], and it is associated with adverse outcomes both during pregnancy as well as later in life [1,2,4-6]. If effective, the HealthyMoms app has potential to be implemented in maternity clinics nationally and offer an evidence-based intervention program to women at relatively low costs. This is of particular importance, given the ubiquity of mobile phone ownership, irrespective of socioeconomic status [10].

## Appendix

Multimedia Appendix 1 Peer-reviewer report 1.

Multimedia Appendix 2 Peer-reviewer report 2.

## Abbreviations

HOMA-IR: homeostasis model assessment - insulin resistance
mHealth: mobile health
